### Controlled interrupted time series analysis

Interrupted time series (ITS) analysis is a valuable study design for evaluating the effectiveness of a population-level health intervention that is implemented at a clearly defined point in time
^27^. It uses a set of historical observations of an outcome of interest (in this context monthly dengue case notifications) to establish an underlying trend, which is assumed to be ‘interrupted’ by the introduction of an intervention (in this case
*Wolbachia* releases). Comparison of the trend in monthly case notifications in the post-intervention period with the hypothetical scenario of no intervention (the ‘counterfactual’, inferred from the historical time series and the untreated control area), provides an estimate of the intervention effect. Segmented regression will be used to estimate the effect of
*Wolbachia* releases on monthly case counts of dengue and chikungunya, using an appropriately defined model: e.g. negative binomial regression for autocorrelated count data with population offset, adjusted for temporal effects using indicator variables or flexible cubic splines, and assuming a step change post-intervention. The
*Wolbachia* intervention effect will be estimated from the interaction between a binary ‘area’ variable (intervention vs control area) and a binary ‘period’ variable (post
*-*intervention
** vs
** pre
*-*intervention). The post-intervention period will be defined for the control area beginning at the same time as the post-intervention period in the comparative release zone. This allows explicitly for a level change in the outcome (dengue case incidence) in both intervention and control areas in the post-intervention period, for example in a scenario where other secular events coincident with the
*Wolbachia* deployments may have influenced dengue incidence in both intervention and control areas independent of
*Wolbachia*. An additional analysis will consider
*Wolbachia* frequency as a continuous covariate or categorised into quintiles of exposure reflecting the measured

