*Wolbachia* prevalence in the local mosquito population. The outcome distribution is assumed to be negative binomial to allow for overdispersion. Robust standard errors will be used to account for autocorrelation and heteroskedasticity. If an excess of zero counts is apparent, the proposed negative binomial model will be nested within a zero-inflated negative binomial model of the same structure. A likelihood ratio test can be performed to test model fit.

Separate analyses will be performed for each release zone compared with its pre-defined control area, and for the aggregate release areas in each city compared with the control area for each city. The availability of comparative control areas – well-matched to the release area in demographic characteristics and historical arboviral disease incidence (
Figure 2 and
Figure 3) – permits a robust, controlled analysis in which the confounding effects of seasonality and inter-annual variability can be adjusted for. The intervention effect will be estimated after 12 months of post-release observations have accumulated, and each 12 months thereafter for five years using cumulative post-release observations, for each release zone individually and in aggregate for each city.

Power was estimated for the ITS analysis using 1000 simulated datasets drawn from a negative binomial distribution fitted to a ten-year time series (2007–2016) prior to
*Wolbachia* deployment, of monthly dengue case notifications from release and control zones in Niterói and Rio de Janeiro. The simulated time series of dengue case numbers in the control zones as well as the pre-
*Wolbachia* release dengue case numbers in the treated zones were drawn directly from this model-generated distribution. Post-

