### Dengue outbreak signals

As a complementary approach for evaluating the public health impact of large-scale
*Wolbachia* releases, we will also use the following dengue outbreak alert tools routinely used in public health practice. We hypothesise that these dengue outbreak signals will not be triggered in areas where
*Wolbachia* has been established.

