^2^, with population >1 million). We also cannot exclude the possibility of a concurrent change in socio-demographic or ecological factors related to dengue risk, or a change in dengue control practices, between the intervention and control areas independent of the
*Wolbachia* intervention, but given the strong synchrony in dengue incidence between intervention and control zones for over a decade prior to releases this is considered unlikely. 

Human mobility also presents a potential challenge to this study, especially during the period in which staged releases are occurring and
*Wolbachia* levels are heterogeneous, as individuals are likely to spend time in both
*Wolbachia*-treated and untreated areas, making it difficult to determine the place of illness acquisition among notified cases of arboviral disease. Travel between areas means that the true
*Wolbachia* exposure status of individuals resident in
*Wolbachia*-treated and untreated areas becomes more similar, thereby diluting the observed intervention effect towards the null.

The introduction of Zika and chikungunya viruses brought new challenges to health surveillance and a greater willingness for better vector control in affected regions. With the re-emergence of yellow fever in Brazil
^8^, there is even more potential public health benefit if the
*Wolbachia* intervention successfully reduces the vector competence of
*Ae. aegypti* mosquitoes in the field and reduces arboviral disease incidence. No specific treatment for dengue, chikungunya or Zika currently exists. Although a vaccine against dengue (Sanofi Dengvaxia
^®^) was licensed in 2015, it was recently found to enhance the severity of subsequent dengue infection in individuals who were seronegative at the time of vaccination. As a result, a serology test prior to the administration of the vaccine is required to confirm previous dengue infection, increasing costs and decreasing feasibility in high-burden areas
^34^.

Releases of
*Wolbachia* are completed or underway in eight countries, with no evidence of local transmission of dengue, Zika or chikungunya in places where
*Wolbachia* is established at high levels
^21^. The implementation of the

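### If the zero-inflated fallback is used, the area-by-period interaction need not be the incidence ratio and can understate the effect when the intervention itself produces the zero months

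*Protocol article*

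**What the plan says.** All of this is in the Protocol article, Methods, Controlled interrupted time series analysis, unless noted.

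- Base model: "The outcome distribution is assumed to be negative binomial to allow for overdispersion", with a population offset, a step change after the intervention and robust standard errors for autocorrelation and heteroskedasticity.
- Effect measure: the "intervention effect will be estimated from the interaction between a binary" area variable and a binary period variable.
- Fallback: "If an excess of zero counts is apparent", then "the proposed negative binomial model will be nested within a zero-inflated negative binomial model of the same structure". Next comes an optional check: "A likelihood ratio test can be performed to test model fit".
- Units of analysis: "Separate analyses will be performed for each release zone compared with its pre-defined control area", plus the aggregate release area of each city, repeated every 12 months for five years on cumulative data.
- Mechanism: the Discussion reports "no evidence of local transmission of dengue, Zika or chikungunya in places where" Wolbachia is established at high levels.

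The article does not say what enters the zero part, which ratio is reported under the fallback, or what counts as an excess of zeros.

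**The concern.** The effect is tied to an interaction coefficient, and the fallback keeps the same structure. Followed as written, the natural reading is that the reported effect becomes the interaction in the count part of the zero-inflated model. That coefficient compares case rates among months that are not structural zeros. The stated objective is the reduction in disease, and the article defines incidence as cases over population, which includes the zero months.

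If releases stop local transmission in some months, those zeros arise in one cell only: treated area, after release. The zero part then absorbs them, and with them part of the benefit. The switch depends on the outcome data, so two zones, or two annual reports on one zone, could carry ratios that mean different things.

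**Working it through.** **The plan's own figure first.** The article states 80% power for a 50% reduction at three years and for a 60% reduction at two years, simulated with a plain negative binomial model. It gives no dispersion k or monthly means, so this cannot be reproduced exactly. A Wald approximation for large means is Var(log RR) = k(2/84 + 2/n_post), with 84 pre-intervention months and two-sided 0.05 (sidedness assumed).
- RR 0.5, 36 post months, k = 0.77: variance 0.77 × 0.0794 = 0.0611, SE 0.247; 0.693/0.247 − 1.96 = 0.84, power 80%. At the same k, RR 0.4 with 24 post months gives 89%.
- k = 1.0: 69% and 80%.

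The stated power is therefore attainable at a plausible k and is not shown to be wrong. It describes the plain model, not the fallback.

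**Identity.** In a zero-inflated model E[Y] = (1 − π)μ, where π is the structural-zero probability. Hence

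overall RR = count-part RR × [(1 − π treated,post)(1 − π control,pre)] / [(1 − π treated,pre)(1 − π control,post)].

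The two ratios agree only if the bracketed terms cancel. With structural zeros in the treated-post cell alone, at π = 0.5 and a count-part RR of 0.80, the overall RR is 0.80 × 0.50 = 0.40.

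**Simulation.** Assumed inputs: k = 0.8, seasonal mean, 84 pre and 36 post months per area, months independent, 150 datasets per scenario. The true overall RR is 0.40 throughout. Entries are median rate ratios.

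| Scenario | Plain NB | Count part, constant zero part | Count part, interaction in zero part |
|---|---|---|---|
| A. Pure NB, mean 20 | 0.41 | 0.41 | 0.41 |
| B. Pure NB, mean 3 (44% zero months, treated-post) | 0.40 | 0.40 | 0.40 |
| F. 20% structural zeros in all four cells | 0.40 | 0.39 | 0.39 |
| C. Effect wholly through structural zeros (π = 0.6), mean 20 | 0.36 | 0.58 | 0.98 |
| D. Mixed (count RR 0.8, π = 0.5), mean 20 | 0.39 | 0.49 | 0.80 |
| E. Mixed (count RR 0.8, π = 0.5), mean 3 | 0.39 | 0.40 | 0.72 |

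A separate simulation, also with a true ratio of 0.40 and intervention-produced zeros, gave plain NB 0.36 to 0.43, and count part 0.63 to 0.86 (interaction in the zero part) or 0.37 to 0.55 (constant zero part).

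**When the switch would occur.** A likelihood ratio test at 9.49 (chi-square, 4 df) favoured the model with the interaction in the zero part in 71% to 100% of datasets in C, D and E, and in 1% to 3% in A and B. It also did so in 100% of F, where no harm follows.

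**Where it could bite.** Populations are from Table 1. Assumed: 50 to 500 notifications per 100,000 per year before the effect, then RR 0.4, k = 0.8, P(0) = (1 + kμ)^(−1/k).
- Niterói Zone 1 (23,747 residents): μ = 23,747 × 50/100,000/12 × 0.4 = 0.40, P(0) = 71%. At 500 per 100,000, μ = 3.96 and P(0) = 17%.
- City aggregates over the same range: 0.7% to 11% in Niterói (373,117) and 0.3% to 4% in Rio de Janeiro (886,551).

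These are ordinary low-count zeros. They show where zero months will be common, not that an excess will exist.

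**The case against.** - **The article never says that only the count-part ratio will be reported.** It also describes the effect as observed notifications against a no-intervention counterfactual, which fits an overall ratio from both parts. This stands: the bias is conditional on what is reported. But the one effect measure named is an interaction coefficient, and an overall ratio is not one. The issue is thus a mismatch between two stated choices, more than a detail left to an unseen analysis plan.
- **A reader might infer that any zone with many zero months is biased.** The documents do not support that. Their trigger is an excess of zeros, and scenarios B and F show no bias.
- **The mechanism fits this endpoint imperfectly.** The primary endpoint is all notified suspected cases under a non-specific definition, assigned by residence, in a mobile population. Notifications would continue after local transmission stops. This largely stands. In one check a background of 0.5 notifications a month removed the bias. In a repeat of scenario D (60 datasets, Poisson background 0.5 in every cell, true ratio (8 + 0.5)/(20 + 0.5) = 0.41) it vanished with a constant zero part (0.39, as in plain NB). It shrank but remained with the interaction in the zero part (0.50).
- **A dramatic example is easy to build.** With 60% structural zeros and a count ratio of 0.75, a true (1 − 0.6) × 0.75 = 0.30 would be reported as 0.75. Those inputs are invented and assume no structural zeros in the other three cells.
- **The outbreak-signal hypothesis is weak support.** "We hypothesise that these dengue outbreak signals will not be triggered in areas where" Wolbachia is established concerns signals, not zero months. At 300 per 100,000, Niterói Zone 1 could have about 71 cases in a month (23,747 × 0.003) without passing the threshold.
- **The likelihood ratio test is optional and no reference distribution is named.** With an intercept-only zero part, ignoring the parameter boundary makes it conservative, against switching. It would be too strong to call the plan's test invalid. What stands is that its ordinary form treats months as independent, while the plan itself allows for autocorrelation.
- **Reach is small.** Niterói Zone 1 holds 23,747 of 1,259,668 treated residents (1.9%), and no formal between-zone comparison is planned.

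**Conclusion.** The point holds in conditional form. If the zero-inflated fallback is used, the excess zeros come from the intervention, and the count-part interaction is reported, the reduction is understated. In the main simulation a true ratio of 0.40 appeared as 0.72 to 0.98 with the interaction in the zero part, and as 0.40 to 0.58 with a constant zero part. Those sizes rest on assumed dispersion, means and structural-zero shares and on independent months. The article supplies none of these inputs, so the direction is firmer than the amount.

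The exposure is in the small-zone analyses and, if modelled the same way, in sparse endpoints such as severe or fatal dengue. A reader might infer that the city-level primary result is at risk; the expected zero-month shares make that unlikely. The point is still worth acting on, because the planned negative binomial model already estimates the intended ratio without the problem.

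**What to change.** Keep the negative binomial mean model, with the robust standard errors already planned, as the effect estimate for every zone and both city aggregates. If a zero-inflated model is fitted, label it a sensitivity analysis and report the overall (marginal) incidence ratio from both parts, with an interval that allows for autocorrelation, such as a block bootstrap. Do not let the likelihood ratio test decide which effect is reported; comparing observed with predicted zero frequencies is enough to describe fit.

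The cost is a few sentences of wording and a little more analysis work if the sensitivity model is run. No new data are needed.

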## Methods

### Study design

The aim of this epidemiological study is to test the hypothesis that the establishment of
*Wolbachia* in local
*Ae. aegypti* populations in Rio de Janeiro and Niterói leads to a reduction in the burden of
*Aedes*-borne disease.

The impact of
*Wolbachia* deployment on disease incidence will be evaluated using routine notifiable disease surveillance data to describe associations between temporal and spatial trends in dengue, chikungunya and Zika and the deployment of
*Wolbachia* across Niterói and Rio de Janeiro, with two objectives:

1. Estimate the reduction in dengue, chikungunya and Zika in the aggregate treated areas of Niterói and Rio de Janeiro compared to an untreated control area, and in each treated zone compared to the untreated control area, each year for five years after
*Wolbachia* establishment.2. Quantify the occurrence of dengue outbreak signals in
*Wolbachia* treated areas compared to untreated areas in Niterói and Rio de Janeiro, for five years after
*Wolbachia* establishment, using outbreak indicators employed routinely for public health monitoring of dengue activity: i) control diagrams comparing the weekly dengue incidence (five-week moving average) against the five-year historical average in that same area; and ii) outbreak incidence threshold of 300/100,000 population in any month.

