### Study setting and population

Rio de Janeiro and Niterói cities are located in the State of Rio de Janeiro, Brazil. Niterói has an area of 134 km
^2^ and a population of 484,918 in 2010. Rio de Janeiro is the second largest city in Brazil with 6,320,446 inhabitants in 2010 and an area of 1,200 km
^2^. The two cities sit on opposite sides of the Guanabara Bay and are linked by a long bridge, which transports a large commuter population between Niterói and Rio de Janeiro.

The cities are divided into health districts, for the purpose of planning and delivering care - ten in Rio de Janeiro and seven in Niterói. In Rio de Janeiro,
*Wolbachia* deployments will be conducted in one of the administrative areas of the city (
Figure 1; produced in ArcMap version 10.5, ESRI, CA), in an area of approximately 90 km
^2^ and with 886,551 inhabitants, 39% of whom live in slums. The total release area in Niterói is approximately 83 km
^2^ covering a population of 373,117 (
Table 1). For the purposes of
*Wolbachia* deployment, the Rio de Janeiro and Niterói intervention areas are each divided into 4 release zones, respectively, which are aligned with neighbourhood administrative boundaries.

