*Wolbachia* release dengue case numbers in the treated zones were drawn from the same model-generated distribution, modified by an additional parameter for an intervention effect of Relative Risks = 0.6, 0.5, 0.4, 0.3. For each of these four ‘true’ effect sizes and a null effect (RR = 1), applied to each of the 1000 simulated time series, the ‘observed’ effect size was calculated from a negative binomial regression model of monthly case counts in the treated and untreated zones, as described above. Post-intervention time periods of 1, 2 or 3 years were simulated, with the pre-intervention period fixed at 7 years. The estimated power to detect a given effect size was determined as the proportion of the 1000 simulated scenarios in which a significant intervention effect (p<0.05) was observed. These simulations indicate 80% power to detect a reduction in dengue incidence of 50% or greater after three years of post-intervention observations, and a reduction of 60% or greater after two years.

The primary endpoint for the ITS analysis will be dengue cases notified to the disease surveillance system. The secondary endpoints will be: a) the count of severe dengue cases reported to the surveillance system, b) the count of fatal dengue cases reported to the surveillance system, and c) chikungunya and Zika cases notified to the disease surveillance system.

Although the historical time series for chikungunya and Zika incidence is short, we will nonetheless describe the incidence during and after
*Wolbachia* deployments relative to the
*a priori* defined non-release control areas for both Niterói and Rio de Janeiro.

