### Dissemination of study results

Based on the results of the power estimation above, the study outcome will be evaluated and reported two years after the completion of releases. The findings will be submitted for peer review and publication in an appropriate open access journal, together with aggregate supporting data.

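### The yearly analyses pool all post-release months under one step-change term, so they do not estimate the effect in any later year and they blunt waning

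*Protocol article*

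**What the plan says.** All references are to the protocol article.

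- **Study design, objective 1.** The clock starts when *Wolbachia* is established, and the reduction is to be estimated for the aggregate treated areas and by zone: "compared to an untreated control area, and in each treated zone compared to the untreated control area, each year for five years after". Objective 2, on outbreak signals, also runs for five years but does not say each year in that way.
- **Controlled interrupted time series analysis, model.** Segmented regression of monthly counts, adjusted for time by "indicator variables or flexible cubic splines, and assuming a step change post-intervention". The effect is the interaction of a binary area variable with a binary period variable, which is one parameter per comparison.
- **Same section, schedule.** The effect is estimated after 12 months of post-release data and "each 12 months thereafter for five years using cumulative post-release observations, for each release zone individually and in aggregate for each city".
- **Same section, areas.** Each city has its own control: "Separate analyses will be performed for each release zone compared with its pre-defined control area, and for the aggregate release areas in each city". Study setting and population gives four release zones per city.
- **Dissemination of study results.** On the strength of the power result, "the study outcome will be evaluated and reported two years after the completion of releases".
- **Current study status.** Releases are expected to finish by the end of 2019, and surveillance data are analysed until 2023.

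**The concern.** The objective, on its plainer reading, wants a series of yearly reductions. The model delivers one number per comparison, re-estimated on a growing window. The figure issued at year 5 is an average over years 1 to 5, and nothing in the time series section isolates the later years.

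This matters for this intervention in particular. The article presents the method as self-sustaining and gives a sustained reduction in disease burden as the programme's purpose (Background and Discussion). Durability is what a health authority would want from years 3 to 5. Under the stated analysis, an effect that has largely faded can still be reported as a strong cumulative reduction, because the good early years stay in the average.

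The time origin also differs. The objective counts from establishment and the analysis counts from release. With staged releases of at least 16 weeks per zone, year 1 need not be the same calendar period in the two sections.

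**Working it through.** **1. The plan's own figure.** The article states 80% power for a reduction of 50% or more after three years and 60% or more after two years, with seven pre-intervention years. This cannot be reproduced, because the monthly means, the dispersion and the area simulated are not given. It can be checked for consistency with a normal approximation on the log rate ratio:

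SE = s × √(1/84 + 1/(12 × post years)), power = Φ(|ln RR| / SE − 1.96)

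Here s is the unknown monthly standard deviation of the area contrast, months are taken as independent, and a two-sided 0.05 level is assumed. The stated results fit together for s between 1.07 and 1.24:
- s = 1.24, RR 0.5, three years: SE = 1.24 × 0.199 = 0.247; power = Φ(0.693/0.247 − 1.96) = 80%.
- s = 1.07, RR 0.5, two years: SE = 1.07 × 0.231 = 0.248; power just under 80%, so 50% is not yet detectable at two years.

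There is no sign of an error in the power statement. The range of s is used in step 4.

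**2. What one step-change term returns when the effect changes.** Illustration: RR 0.30 in years 1 to 3 and 0.80 in years 4 and 5, with equal baseline incidence each year. The pooled term lies near the arithmetic or the geometric mean, depending on how the fit weights months.
- Arithmetic: (3 × 0.30 + 2 × 0.80)/5 = 2.5/5 = 0.50.
- Geometric: exp[(3 ln 0.30 + 2 ln 0.80)/5] = exp[(−3.612 − 0.446)/5] = exp(−0.812) = 0.44.

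| Report at year | True RR that year | Cumulative, arithmetic | Cumulative, geometric |
|---|---|---|---|
| 3 | 0.30 | 0.30 | 0.30 |
| 4 | 0.80 | 0.425 | 0.38 |
| 5 | 0.80 | 0.50 | 0.44 |

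A steeper case, with yearly RRs of 0.3, 0.3, 0.5, 0.8 and 1.0, gives cumulative values of 0.30, 0.30, 0.37, 0.48 and 0.58 (arithmetic; 0.51 geometric at year 5). The year-5 report would show about a 42% reduction in a year with no effect.

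**3. Can the yearly effect be recovered from the drift?** In the first example, yes, under equal baselines and arithmetic weighting: 5 × 0.50 − 4 × 0.425 = 0.80. If the fit weights geometrically and the same rule is applied, the answer is wrong: 5 × 0.444 − 4 × 0.383 = 0.69. Equal baselines are also unlikely where epidemics come every 2 to 5 years, and differencing published estimates gives no interval.

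**4. Precision of a year-specific term.**
- One year: √(1/84 + 1/12) = 0.309, so SE = 0.33 to 0.38. A 95% interval multiplies and divides the estimate by 1.9 to 2.1.
- Five pooled years: √(1/84 + 1/60) = 0.169, so SE = 0.18 to 0.21 and the factor is 1.4 to 1.5.
- Ratio of log widths: 0.309/0.169 = 1.8, whatever s is.

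In the first example, the pooled year-5 estimate of 0.44 to 0.50 would have an upper limit of at most 0.50 × 1.51 = 0.75. The year-5 term of 0.80 would have an interval of 0.42 to 1.53 (s = 1.07) or 0.38 to 1.69 (s = 1.24). That is wide, but it excludes the early 0.30 and includes no effect. A single year reaches 80% power only for an RR of about 0.34 to 0.40 or lower, which is why estimates with intervals suit these terms better than tests.

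**The case against.** **Each year may mean that an estimate is made every year.** On that reading the cumulative schedule carries out the objective. The wording allows it, so this is not a flat contradiction. The two sections still need reconciling, because a reader cannot tell which quantity is promised and the time origins differ.

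**Waning is not invisible.** Successive cumulative estimates would drift upwards. Outbreak signals are counted per year, as are months above the incidence threshold. A further analysis uses measured *Wolbachia* frequency, so waning through loss of *Wolbachia* is partly addressed. All of this stands and rules out saying that waning is hidden. But the outbreak counts are descriptive, and the frequency analysis models mosquito prevalence rather than time, so it would miss waning at stable prevalence.

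**Pooling is defensible.** Single years may have little transmission, and Niterói Release Zone 1 has only 23,747 residents. This is a good reason to keep the pooled estimate, but not to report it alone.

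**Stronger readings a reader might infer.** One is that no evaluation time is named. The dissemination section does name one, justified by the power result: two years after releases are completed. Another is that eight zones plus two city aggregates at five yearly reports make fifty uncontrolled tests. The document does not support that either. The analysis section speaks of estimating effects, and the 0.05 level appears only as the simulation criterion ("a significant intervention effect (p<0.05) was observed"). Fifty is also an upper limit, since zones finished at the end of 2019 have about four years of data by 2023. Multiplicity rules and the choice of a primary comparison may sit in an analysis plan that is not shown.

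**Conclusion.** The point holds as a gap between the objective and the estimate. The stated model is a single step change fitted to cumulative data. It returns an average over post-release time and does not estimate the effect in any given later year. In the illustration, a late effect of 0.80 is reported as about 0.44 to 0.50 at year 5, or 0.38 to 0.425 at year 4, the last report the latest zones can reach.

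These sizes rest on assumed yearly effects and equal baseline incidence. They are not a prediction that the effect will wane. The precision figures rest on independent months and a back-calculated s, and autocorrelation would probably widen the intervals. The conclusion covers blunted waning, ambiguous wording and a mismatched time origin. It does not extend to a missing evaluation time or an inflated error rate. Improving the analysis is worthwhile because durability is central to the programme, but the pooled estimate itself is not invalid.

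**What to change.** 1. Keep the pooled cumulative estimate. Beside it, fit a model in which the single area-by-period term is replaced by area-by-year-since-intervention terms, for each zone and each city aggregate.
2. Report these as year-specific rate ratios with confidence intervals, without significance claims.
3. Use one time origin, release or establishment, in both objective 1 and the time series section. If it is establishment, define it operationally. Say whether each year means a year-specific reduction or an annual update.
4. Optionally, add one sentence saying that the two city aggregates at the report two years after completion of releases are the lead comparisons.

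**Cost.** No new data are needed, only analysis work and a clearer definition of the time origin. Single-year intervals will be about 1.8 times as wide on the log scale as the five-year pooled interval, and wider again in small zones and low-transmission years. Some year-by-zone terms may be too imprecise to interpret, and the city aggregates will carry most of the information on durability.
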